### Potential Risk Factors

As the study is primarily retrospective, multiple initial information data will be collected and outcome data will be divided into one dimension: new-onset diabetes. Initial information data for five broad categories include (I) demographic information; (ii) medical history; (iii) diagnostic testing; (iv) PCI surgery-related information; and (v) medication situation. Detailed information refer to previous studies on risk factors for diabetes (27, 28) (Table 2). Variables with missing data other than demographic information (age, sex, ethnicity, marital status) will be dealt with using multiple imputation (29).

**Table 2 T2:** Patient information to be extracted.

**Patient information**	
Demographic information	age, sex, ethnicity (nationality/ethnic minorities), marital status, Occupation (physical and non-physical)
Medical history	the type of ACS (STEMI, NSTEMI, UA), smoking history, alcohol consumption history, history of hypertension, history of hyperlipidemia, history of chronic diseases, family history of T2DM, family history of CAD
Diagnostic testing	height, weight, body mass index (BMI), blood pressure, resting heart rate, fasting blood glucose, HbA1c, serum uric acid level, triglyceride level, total cholesterol level, low density lipoprotein level, left ventricular ejection fraction (LVEF)
PCI surgery-related information	number of diseased vessels, number of stent implantation, total length of the stent
Medication situation	statin medications (low intensity, high intensity), traditional Chinese medicine (Yes or No)

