We propose leveraging advancements in machine learning by systematically comparing different modeling approaches (21), to develop a prognostic tool for NODAP. Therefore, we put forward the following hypothesis:

Refer to common risk factors such as obesity and smoking and explore the risk factors for NODAP; probing the risk of NODAP in different types of ACS patients (STEMI, NSTEMI, and UA) is equal or not.Systematically apply several machine learning algorithms to establish a predictive model of NODAP and verify its effectiveness.In this study, we sought to investigate the potential predictors of ACS patients with NODAP and comparatively evaluate performances of these predictive models with each other, to identify which is the most accurate.

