**Exclusion criteria**	
i	Have received coronary artery bypass grafting (CABG)
ii	Patients with severe hepatic and renal insufficiency, severe respiratory, hematonosis, tumor, autoimmune diseases, or multiple organ failure
iii	Patients with Alzheimer's disease, mental illness, or depression
iv	Being pregnant or lactating
v	Did not take secondary prevention^#^ for coronary heart disease after PCI (26)
vi	Participating in other clinical trials

* *Diagnostic criteria for diabetes: fasting blood glucose greater than 7.0 mmol/ L, HbA1c ≥6.5% (23)*.

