### Data

The data extracted from the hospital information system (HIS) will exclude the privacy of participants; detailed parameters will vary based on each institution, which may include outpatient and inpatient medical history and diagnostic imaging database. To ensure the unified management of mass data among multiple institutions, we have established a third-party data management platform (*http://121.30.232.162:10094/#/user/login?redirect=%2F*). Every participant will be assigned a systemic number separate from the medical record number. Based on the platform, the required information can be retrieved and excluded. After machine retrieval by a third-party platform, two researchers will review each participant for inclusion in the study.

Using data provided from decision support at four hospital sites, we expect at least eligible patients in the period 2010–2021, and data according to the fields included in the diagnosis (acute coronary syndrome, PCI, diabetes, etc.) and CCCDNCE 2.0 codes. A standardized case report form (CRF) that has been pilot tested and refined will be used for data extraction. Trained researchers will enter the identified data directly using the electronic CRF into the online platform managed in Beijing, China.

Data will be collected with traditional Chinese and western medicine characteristics that are important in the management of ACS patients with NODAP to confirm the baseline level and severity of blood stasis syndrome. Data will be included in two stages. First, ACS patients who were eligible for inclusion criteria were included. All these patients will be re-screened to ensure the duration of 12 months of follow-up and above. Structural data such as demographic information, diagnostic testing and medication situation can be directly collected in the database. Medical history and surgery records will be retained in the platform in unstructured text format. Researchers in charge of each institution will ensure consistency on extraction method and content, and train individuals for data identification and extraction, and entering DE identified data using the electronic CRF. Relevant medical history including history of ACS, history of T2DM, history of PCI surgery will be collected to confirm the diagnosis. New-onset diabetes was diagnosed by fasting blood glucose or HbA_1_c levels in the outpatient or inpatient biochemical test during follow-up.

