### Statistical Analysis

Baseline demographic characteristics and study outcomes conforming to normal distribution were expressed as mean ± standard deviation. The *t*-test was used for comparison between the two groups. The measurement data not conforming to normal distribution was represented as the median (quaternary interval), and the comparison between the two groups was performed using the Mann–Whitney *U* test. Descriptive statistics will be used for the overall cohort and aggregated statistics will be calculated. Descriptive statistics are used for the entire queue and the aggregated statistics are calculated. Enumeration data were expressed as frequency or percentage, and χ*2* test was used for comparison between the two groups. Univariate analysis was conducted for all factors first, and statistical learning methods such as tree integration algorithm and Lasso regression were adopted to compare and screen related risk factors from multi-dimensional perspectives. To avoid omission of important variables, covariates with *P* < 0.01 in univariate analysis and important factors screened by statistical learning method were included in multivariate logistic regression analysis. Independent risk factors for NODAP were analyzed by progressive forward regression analysis, and the OR value of each related factor and its 95%CI were estimated. *P* < 0.05 on both sides of all tests indicated statistically significant differences.

We will evaluate the potential predictors of NODAP informed by prior literature (10, 20). The data set will be randomly divided into a training dataset and an internal validation dataset in a 5:5 ratio. We will include all a priori selected variables in the final model; the Bootstrap method was used for model internal validation in this data set. If necessary, non-normally distributed variables will be transformed using the Box-Cox transformation. The validation will be established with the same inclusion and exclusion criteria and sensitivity analyses will be performed. All analyses were performed using R3.6.1 and SPSS^®^ Statistics 21 software (IBM^®^, Armonk, NY, USA). Prism 5 (GraphPad Software Inc., San Diego, CA, USA) is used for drawing statistical graphs.

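### One forward-selected model, with baseline fasting glucose and HbA1c among its candidates, serves both aims, so ORs for upstream factors such as obesity can be attenuated or dropped

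*Protocol article*

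**What the plan says.** The Introduction states two aims. The first is explanatory in wording: "Refer to common risk factors such as obesity and smoking and explore the risk factors for NODAP", and it also asks whether risk differs between ACS types. The second is predictive: "Systematically apply several machine learning algorithms to establish a predictive model of NODAP and verify its effectiveness".

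The Statistical Analysis section gives one route to the reported ORs. It starts with a screen ("Univariate analysis was conducted for all factors first"). Factors with univariate P < 0.01, or picked by tree or Lasso methods, go into a multivariable logistic model. Then: "Independent risk factors for NODAP were analyzed by progressive forward regression analysis", with an OR and 95% CI for each factor. The section also says that variables chosen in advance will be in the final model, but does not list them. No separate risk-factor model is described.

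Table 2 names the candidates. Under diagnostic testing it has "resting heart rate, fasting blood glucose, HbA1c, serum uric acid level", in the same list as BMI; age, family history of diabetes and statin intensity stand in other rows. The Data section defines the outcome on the same markers: "New-onset diabetes was diagnosed by fasting blood glucose or HbA_1_c levels in the outpatient or inpatient biochemical test during follow-up". The note to Table 1 sets the diagnostic limits that patients must not have met before PCI: "fasting blood glucose greater than 7.0 mmol/ L, HbA1c ≥6.5"%.

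**The concern.** Baseline fasting glucose and HbA1c are earlier readings of what later defines a case. They also plausibly lie between obesity, family history or age and the outcome. An OR for BMI adjusted for both describes how BMI relates to NODAP among patients equally close to the diagnostic limit. That is a sound quantity for prediction, but it leaves out any part of the BMI association that runs through baseline glycaemia.

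Forward selection adds a second step. A factor whose adjusted association has become small can fail to enter, and is then missing from the list of independent risk factors. A reader interested in the first aim may take that absence to mean that obesity does not matter, when its association is carried by a marker in the same model. The point concerns the ORs and the list of factors. It does not concern the AUC or the use of glycaemia as a predictor.

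**Working it through.** **1. The plan's own figures.** The Sample Size section gives 10,000 to 15,000 procedures and 6.1-11.6% NODAP.
- Minimum events: 10,000 × 0.061 = 610, as stated.
- Half under the 5:5 split: 610 / 2 = 305, against the stated 300 per set. The 300 also equals the 30 variables counted in Table 2 (5 + 8 + 12 + 3 + 2) at 10 events each.

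**2. Will glycaemia enter the model?** For a standardised covariate, the SE of the log OR is about 1/√(N·p·(1−p)).
- With N = 5,000 (half of 10,000) and p = 0.061: SE = 1/√(5,000 × 0.061 × 0.939) = 0.059.
- For an assumed OR of 1.3 per SD: z = ln(1.3)/0.059 = 0.262/0.059 ≈ 4.4, well beyond 2.58 (P < 0.01).
- The expected z falls to 2.58 when N·p·(1−p) = (2.576/0.262)² ≈ 96, which is about 103 events at 6.1%.

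This treats all 10,000 procedures as eligible and reads 300 per set as NODAP cases. If 300 meant patients, a set would hold 300 × 0.061 ≈ 18 to 300 × 0.116 ≈ 35 events, and z would be only 1.1 to 1.5. The Lasso or tree screen and the unlisted prespecified variables are further ways in. The Abstract also names impaired glucose tolerance as a known risk factor. Entry is therefore very likely at the intended size, but it is not stated.

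**3. What happens to the BMI OR if glycaemia enters?** This was checked by logistic simulation. None of the following inputs except the event rate and the half-cohort size comes from the article:
- N = 5,000 and 6.1% events.
- Assumed total BMI OR of 1.35 per SD.
- Assumed BMI-glycaemia correlation of 0.2 or 0.3.
- Fasting glucose and HbA1c as two noisy measures (reliability 0.8) of one glycaemia variable.
- Runs with and without exclusion of high baseline values, 150 per setting.

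The share of the BMI effect passing through baseline glycaemia was varied. The loss is 1 − ln(OR with)/ln(OR without), taken within each setting.

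| Assumed mediated share | OR without glycaemia | OR with glycaemia | Log OR lost | Power at 0.05, without → with |
|---|---|---|---|---|
| 0% | 1.34-1.36 | 1.34-1.36 | none | 0.99-1.00 → 0.99-1.00 |
| 25% | 1.32-1.34 | 1.26-1.27 | 14-21% | 0.99-1.00 → 0.96-0.99 |
| 50% | 1.28-1.34 | 1.18-1.19 | 30-43% | 0.99-1.00 → 0.75-0.86 |
| 75% | 1.23-1.34 | 1.10-1.11 | 50-65% | 0.93-1.00 → 0.33-0.38 |
| 100% | 1.18-1.32 | 1.03-1.04 | 76-88% | 0.80-1.00 → 0.07-0.09 |

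Example at 50%: from 1.34 to 1.18, 1 − 0.166/0.293 = 43%. The small residue at 100% arises because the two markers measure glycaemia with error. The power column indicates how often a single BMI test reaches 0.05. The full forward selection over 30 candidates was not simulated, and only BMI was modelled.

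**The case against.** The strongest reply is that the mutually adjusted OR is what the article asks for. It looks for independent risk factors, describes its purpose as finding potential predictors, calls the analyses exploratory and claims association only. On that reading, reporting that BMI adds nothing once glucose is known is a correct answer. This stands as a defence of the conditional OR as a quantity. It does not help a reader of the first aim, who sees one OR without a label saying that it is conditional on glycaemia.

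A second reply is that the univariate step already gives associations unadjusted for glucose. It does, so an association carried by glucose need not go unseen. But the step serves as a screen, no OR is promised for it, and it is not adjusted for age, sex or other confounders. The confounder-adjusted OR without glycaemia is still missing.

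A third reply concerns the remedy, and it stands. Leaving out glycaemia does not give a total effect, since lipids, uric acid and blood pressure may lie on the same pathway. For statin intensity after PCI, baseline glycaemia comes before the exposure and may confound, so removing it could make that OR worse.

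A reader might go further and infer that real risk factors will be reported as weak or absent. The documents do not support that. They give no mediated share, factors that act by other routes keep their OR, and near-null results appear only when almost all of the effect runs through glycaemia. Nor do they say outright that the final ORs are adjusted for both markers.

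**Conclusion.** The point holds as a mismatch between the first aim and the only modelling route described. If fasting glucose and HbA1c enter, ORs for upstream factors are conditional on baseline glycaemia; they can be attenuated, and forward selection can drop the factor. Under the stated assumptions the loss runs from none at a 0% mediated share, through 30-43% of the log OR at 50%, to 76-88% at 100%. The article does not allow a choice within that range. Very likely entry rests on roughly 305 events per half and an assumed glycaemia OR of at least 1.3 per SD. The plan should be changed because the change is cheap and answers the first aim better. The prediction model is not at fault for containing these markers.

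**What to change.** - Keep baseline fasting glucose and HbA1c in the prediction model.
- For the first aim, prespecify the named factors and confounders. Show two sets of confounder-adjusted ORs side by side, with and without the two markers, and do not let forward selection remove the named factors. Label the first set *conditional on baseline glycaemia*.
- Do not describe a factor as not being a risk factor on the strength of the glycaemia-adjusted model alone.
- For statin intensity after PCI, keep the glycaemia-adjusted OR as the main one.
- State that the ORs without glycaemia are not total causal effects, because other candidates may also be mediators.

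The cost is one extra model and one table column, from data already to be collected.

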## Abstract

**Background:** Type 2 Diabetes mellitus (T2DM) is a major risk factor for cardiovascular diseases and increase mortality. Clinical outcomes of patients after percutaneous coronary intervention (PCI) were worse in T2DM patients than those without T2DM. New-onset diabetes after PCI (NODAP) is often observed during long-term follow-up and this further aggravates cardiovascular diseases. Several studies had focused on patients after PCI with known T2DM. Previous studies showed that impaired glucose tolerance and aging are risk factors that promote NODAP. Considering the unique characteristics of patients after PCI, we will further study relevant risk factors. We sought to investigate the potential predictors of acute coronary syndrome patients with NODAP by a multicenter retrospective cohort study.

**Methods:** This is a multicenter retrospective cohort study including patients after PCI. Clinical medical records of these patients were collected from four hospitals in different areas in China, from 2010 to 2021. Patients' demographic information, medical history, diagnostic testing, PCI-related information, medication situation will be summarized using descriptive statistics, and correlation analysis was performed on the development of new-onset diabetes. Variation will be described and evaluated using χ^2^ test or Kreskas-Wallis test. The prediction model will be verified by a validation set.

**Discussion:** A novel diabetes prediction model for patients after PCI is established, and this study can achieve advanced intervention for the occurrence of NODAP. Owing to its retrospective nature, this study has some limitations, but it will be further studied through supplement data collection or prospective study. The study has been registered for clinical trials by the Chinese Clinical Trial Registry (**ChiCTR2100047241**).

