## Introduction

Type 2 Diabetes mellitus (T2DM) is a major health concern worldwide, with a prevalence of about 463 million by 2019, and a 62% increase since 2009 (1). In Chinese adults, the estimated T2DM and pre-T2DM prevalence are 10.9% and 35.7% (2), respectively. It is a strong risk factor for cardiovascular artery disease (CAD) and major adverse cardiovascular events (MACE) (3–5). A pooled analysis involving more than 1 million participants in Asia found that patients with T2DM had a higher risk (hazard ratio, 1.89) of all-cause death than those without T2DM (6). People are conferred an eight fold increase in death risk by unrecognized myocardial infarction (MI) with diabetes (7). As patients with acute ST-segment elevation myocardial infarction (STEMI) significantly improved after percutaneous coronary intervention (PCI), the 10-year survival rate was nearly 76% (8). Prolonged life expectancy makes chronic care management after PCI a concern. Nearly half of the inpatients with MI complicated with T2DM (9, 10) and good blood glucose control is one of the keys. There have been multiple studies regarding clinical outcomes in patients after PCI with known T2DM (11, 12). Patients after PCI with chronic T2DM emerge with poor clinical outcomes and different treatment strategies (13, 14). Patients approximately 30% who underwent PCI suffer from diabetes (13). Considering the counter-balancing effects of hemorrhagic and ischemic complications, the recent ultra-short DAPT strategy may not be suitable for patients with T2DM (15). New-onset of diabetes after PCI (NODAP) has attracted much attention; a 5-year survival of patients after revascularization with diabetes were worse (16). Among 3,683 acute coronary syndrome (ACS) patients (without T2DM before PCI), 436 patients (11.8%) developed NODAP after a follow-up of 3.41 ± .9 years (10).

However, the risk factors and pathophysiological mechanisms for NODAP remain unknown. The risk factors for NODAP may be different from those for simple diabetes. Patients after PCI are generally elderly, and are associated with a variety of metabolic diseases (obesity, hyperlipidemia, etc.) and stress states related to surgery; all the above predict the risk of T2DM. Previous studies show that abnormal heart rate variability is a risk factor for diabetes (17), and heart rate variability (low SDNN) is common in patients undergoing PCI (18). High intensity statins (19, 20) also has adverse effects on diabetes.

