**Inclusion criteria**	
i	Age > 18 years
ii	Adults with a primary diagnosis of an ACS (23)
iii	Did not meet the diagnostic criteria for diabetes (24, 25) before the PCI surgery^*^, no history of taking hypoglycemic drugs or insulin
iv	Only have received the initial PCI
v	outpatient follow-up ≥12 months
vi	Volunteer to participate in the study

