## Discussion

### Strengths

The protocol for the study design and methods to evaluate a new model of patients with new-onset diabetes mellitus after PCI. This study represents the largest cohort study that addresses risk factors for NODAP and it will make available data as regards blood glucose management and T2DM risk prediction. Prior studies carried out in Taiwan (20) were based on a health insurance database and the use of statin was the only variable that was extracted; all subjects in the large academic tertiary care hospitals can be a source of bias. With increases in aging, more people will be diabetic after PCI over a long period. This proportion will continue to increase, emerging sensitive predictors (35). This is the first study that addresses the risk factors for diabetes after PCI. The related factors of PCI surgery were reviewed, and a more comprehensive evaluation of diabetes after PCI was performed.

A future direction for the study is to collect patient-reported outcomes through the questionnaires to supplement the retrospectively available data, or to conduct a prospective cohort study where data will be collected at baseline and at 12-month follow-up, pending additional institutional review board (IRB) approval. Consent forms will be distributed to participants before data collection. Consent forms will highlight the voluntary nature and anonymity of the participation. Based on the above studies, our study went further to verify the risk factors, incidence and prognosis of T2DM after PCI.

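### The cohort pools about 11 years of first PCIs with open-ended follow-up, but no PCI date is listed and no year or follow-up term enters the logistic models, so calendar-time differences may pass into the reported odds ratios

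*Protocol article*

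**What the plan says.** The Abstract of the protocol article states: "Clinical medical records of these patients were collected from four hospitals in different areas in China, from 2010 to 2021". The Data section repeats the window: "we expect at least eligible patients in the period 2010–2021". Table 1 requires "outpatient follow-up ≥12 months" and sets no upper limit. Outcomes Measures defines the outcome as the occurrence of NODAP and again gives 12 months as a minimum.

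Table 2 sets out the information to be extracted in five groups. The procedural group is "number of diseased vessels, number of stent implantation, total length of the stent". The medication group is "statin medications (low intensity, high intensity), traditional Chinese medicine (Yes or No"). Neither these nor the other three groups contain the date or year of PCI, or length of follow-up.

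Under Statistical Analysis, factors with univariate P < 0.01 and "important factors screened by statistical learning method were included in multivariate logistic regression analysis". Forward selection then yields odds ratios with 95% confidence intervals, reported as independent risk factors. The data are halved at random for development and validation. Sensitivity analyses are promised but not described. The Limitations section does not mention calendar time.

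**The concern.** Year of PCI can be linked to the outcome in two ways. The underlying risk of NODAP, or the intensity of testing for it, may change over a decade. Separately, if patients are followed for as long as records allow, a 2010 patient has many more years in which to be diagnosed than a 2020 patient. A logistic model of whether NODAP ever occurred treats the two alike.

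If a factor's use also changed with year, part of that link appears in its odds ratio. Treatment choices such as statin intensity, stent number and length, and Chinese medicine could plausibly change over such a span. Identifying risk factors is the study's first aim, so a false or distorted one bears on the main result. The prediction tool would also carry a baseline risk averaged over the whole period and over mixed follow-up. A random split gives both halves the same mix of years, so internal validation would look sound either way.

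**Working it through.** **The plan's own figures.** Sample Size gives 10,000 PCIs at the lower end and a NODAP rate of 6.1%: 10,000 × 0.061 = 610 events, as stated. Half is 305, against a stated 300 per set. Table 2 lists 5 + 8 + 12 + 3 + 2 = 30 variables, and 30 × 10 events per variable = 300, which agrees.

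**Span.** With records to 2021 and 12 months of follow-up required, index PCIs run from 2010 to about 2020, which is 11 yearly cohorts.

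**Method.** Take a binary factor with no effect within any year. Let p_y be its prevalence and r_y the NODAP risk in year y, with equal yearly cohorts. Then

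crude OR = [Σp_y r_y · Σ(1−p_y)(1−r_y)] / [Σp_y(1−r_y) · Σ(1−p_y)r_y],

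and z = ln(OR)/SE, with SE = √(1/A + 1/B + 1/C + 1/D) from the expected cell counts. All drift values below are assumptions. N = 10,000 is the lower PCI count before exclusions, and 5,000 is half of it.

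**(a) No change in the factor's use** (40% throughout): OR = 1.00, and 5% of tests fall below 0.05.

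**(b) Risk drifts and follow-up is equal** (mean risk 6.1%, N = 10,000):

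| Yearly factor on odds | Use 30%→50%: OR, P(p<0.05) | Use 20%→60%: OR, P(p<0.05) |
|---|---|---|
| 1.03 | 1.03, 6% | 1.05, 9% |
| 1.05 | 1.04, 8% | 1.08, 16% |
| 1.10 | 1.08, 15% | 1.17, 45% |

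With N = 5,000 the last column falls to 7%, 10% and 25%.

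**(c) Constant hazard of 1% a year, everyone followed to the end of 2021.** With PCI at mid-year, r_y = 1 − exp[−0.01 × (2021.5 − y)]. This gives 10.9% for 2010, 1.5% for 2020 and a mean of 6.2%, close to the plan's 6.1%.

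- Use 30%→50%: risk is 5.78% in users and 6.56% in non-users. OR = (0.0578/0.9422)/(0.0656/0.9344) = 0.87. P(p<0.05) is 20% at N = 5,000 and 35% at N = 10,000.
- Use 20%→60%: risks are 5.31% and 6.87%. OR = (0.0531/0.9469)/(0.0687/0.9313) = 0.76. P(p<0.05) is 61% and 88%. At N = 10,000, z = −3.15, beyond the 2.58 needed for the P < 0.01 screen.

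**(d) Both together.** With hazard 0.01 × 1.05^(y−2015) and use 20%→60%, the risks are 5.22% and 6.32%, so OR = (0.0522/0.9478)/(0.0632/0.9368) = 0.82. The two routes partly offset each other here but do not cancel.

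**Room for extra terms**, counting one parameter per variable: one linear year term gives 31 parameters and 305/31 = 9.8 events per variable in one half, or 610/31 = 19.7 overall. Two extra terms give 305/32 = 9.5, and three give 305/33 = 9.2.

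**The case against.** The strongest reply is that this is an article whose full analysis plan is not shown, and that a period term is often left to such a plan. The PCI date must be available to apply the 12-month rule, the promised sensitivity analyses might cover it, and the Limitations call the work exploratory and associational. This is why the point is a recommendation. It does not dispose of it: the article fixes the variable list, the selection route and the label of independent risk factors, and none of the three has a place for calendar time.

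A reader might infer that calendar drift *will* be reported as stent or drug effects. The documents do not support that:

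- The Introduction's figure, "with a prevalence of about 463 million by 2019, and a 62% increase since 2009", is a worldwide count of people with diabetes, not a NODAP rate. Even if it is borrowed as a trend (1.62^(1/10) = 1.049 a year, mean risk 8.85%, twelve yearly cohorts), a null factor rising from 20% to 70%, or from 10% to 80%, has a crude OR of 1.12 or 1.17. With an assumed 7,000 patients, z is only 1.4 or 1.9.
- In Strengths, "This proportion will continue to increase" follows a sentence about ageing, and age is in Table 2.
- The recent change in care that the Introduction mentions concerns antiplatelet duration, which is not a Table 2 variable. Nothing shows that any listed factor changed in use.

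The odds ratios above are also crude. Adjusting for age, BMI, fasting glucose and HbA1c could absorb some of the risk drift, but no listed variable measures time at risk.

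Finally, Outcomes Measures says that onset falls mainly within the first year, and the Limitations speak of a 12-month follow-up period. If the outcome were read at 12 months, scenario (c) would vanish. Elsewhere, however, 12 months is only a minimum, and the Limitations concede that it is too short for all cases to appear.

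**Conclusion.** The concern holds as a risk of bias, not as a demonstrated bias. The list of variables and the models leave out calendar year and follow-up time in a cohort spanning about 11 years, and the random split cannot detect the consequence. Bias needs both the factor's use and the recorded NODAP risk to shift with year; the documents quantify neither.

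Under the stated assumptions a factor with no effect has a crude OR from 1.00 (stable use) to about 1.03–1.17 (risk drift) or about 0.76–0.87 (unequal follow-up). The direction is therefore undetermined. Unequal follow-up is the better grounded route, because it follows from an open-ended follow-up rule under a logistic model, and only there did a scenario pass the P < 0.01 screen on expected z. It still rests on the assumed 1% hazard, on follow-up running to the end of 2021, and on a marked change in use.

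**What to change.** 1. Add the index PCI date to Table 2.
2. Force year of PCI (linear, spline or 3–4 year bands) into every risk-factor model, outside the selection step.
3. Deal with unequal follow-up by one of: a fixed 12-month outcome; a time-to-event model; or a follow-up-time term, defined as observation time available and not time to diagnosis. If everyone is followed to the same closing date, that term and year are nearly the same variable, so one of the first two is cleaner.
4. Report NODAP by period of PCI, and show predicted against observed risk in the latest years before offering the prediction tool for current patients.

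Cost: 1–3 degrees of freedom for year, some extra analysis and no extra patients; the date is already needed to check eligibility. A fixed 12-month outcome can lose events. At the assumed 1% hazard, 10,000 × (1 − e^−0.01) ≈ 100 would remain of about 610, although far fewer would be lost if onset is mainly in the first year as the protocol says. A time-to-event model keeps them all.
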